#### 2.7.2. Qualitative Scoring of Changes on Cardiac SPECT

Postradiotherapy cardiac SPECT will be compared to baseline to assess changes in cardiac perfusion. Increases in SSS or SRS ≥ 3 points in one segment or ≥ 2 points in at least two segments between post- and pre-RT scans will be considered clinically significant.

#### 2.7.3. Assessment of Ventricular Ejection Function

The QGS/QPS Cedars-Sinai software will automatically calculate left ventricular ejection fractions (EFs). This will be accomplished by estimating the LV endocardial surface throughout the cardiac cycle and calculating LV volumes as the sum of the voxels within the contours of each frame. End-diastolic and end-systolic volumes will be determined from the LV volume curves, and EFs will be calculated accordingly.

#### 2.7.4. Assessment of Wall-Thickness Abnormality

The presence or absence of wall-motion abnormalities will be noted for each of the 17 cardiac segments, with any wall-thickness abnormalities visually categorized as hypokinetic, akinetic, or dyskinetic. The size of the affected wall (a small or large portion) will be classified as mild or severe.

#### 2.7.5. Dosimetric Data

Dosimetric parameters that will be collected are: mean dose (Dmean), maximum dose (Dmax), and minimum dose (Dmean) for all substructures; V5Gy and V25Gy for cardiac cavities (left atrium, left ventricle, right atrium, right ventricle); V30Gy and V40Gy for coronary arteries (left main coronary artery, left anterior descending artery, left circumflex artery, right coronary artery), according to DEGRO breast cancer expert panel constraints [42]. Data will be extracted manually from the Varian Eclipse treatment planning system (Varian Medical Systems).

#### 2.7.6. Clinical Data

Other clinical data will be collected during consultation, from clinical exams, and from medical files.

#### 2.7.7. Data Management

Data will be collected and managed with the use of the clinical data management system CleanwebTM.

### 2.8. Statistical Analysis

#### 2.8.1. Sample Size

The estimation of the anticipated incidence of perfusion defects is approximately 17%. The two radiotherapy techniques evaluated (DBIH and IMRT) reduce heart exposure to irradiation. The objective of this dose reduction is to reduce the incidence of perfusion defects to 0%. Assuming an α of 0.05 and 80% power, and since two irradiation techniques are evaluated, the study should include at least 58 subjects to ensure adequate power and compensation for possible loss of patients during the protocol (Rosner B. Fundamentals of Biostatistics, 7th ed., Boston, MA: Brooks/Cole).

#### 2.8.2. Statistical Methods

Medians, proportions, and percentages will be used to describe the population and resulting observations.

The incidence of perfusion defects on follow-up cardiac SPECT will be calculated based on the number of patients with an increase in SSS or SRS ≥ 3 points in one segment or ≥2 points in at least two segments between post- and pre-radiotherapy cardiac SPECT. For comparison among cardiac SPECT results at different time points, the Wilcoxon rank-sum test will be used. The Bonferroni technique will be applied to account for multiple comparisons. Spearman rank correlation will be employed to examine the link between cardiac SPECT changes at 6 months and irradiated heart structures. A univariate linear regression analysis will be conducted to investigate the association between various cardiovascular risk factors and alterations in cardiac SPECT defects. Standard proportional hazard regression analysis will be used for the subsequent multivariate analysis. A *p* value of 0.05 will be considered indicative of statistical significance.

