### 2.5. Objectives

#### 2.5.1. Primary Endpoint

The primary outcome measure of this study is the occurrence of perfusion defects on cardiac SPECT scans during follow-up periods of 3, 6, and 12 months after radiation therapy.

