## 4. Conclusions

If the hypothesis of the absence of perfusion defects is confirmed, then the benefit of the use of these two irradiation techniques will be real and could be considered as new references.

Cardiac follow-up is regularly questioned after breast radiotherapy; if these techniques show no negative impact, specific post-irradiation monitoring will probably no longer be necessary.

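### The sample size rests on a powered contrast of 17% versus 0%, but the stated analysis only calculates the incidence, so it cannot support the conclusion that defects are avoided

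*Protocol article*

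**What the plan says.** All references are to the protocol article.

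- **Section 2.5.1 (Primary Endpoint):** "The primary outcome measure of this study is the occurrence of perfusion defects on cardiac SPECT scans during follow-up periods"; the scans fall at 3, 6 and 12 months.
- **Section 2.8.1 (Sample Size):** "The estimation of the anticipated incidence of perfusion defects is approximately 17" percent, and "The objective of this dose reduction is to reduce the incidence of perfusion defects to 0" percent. The error rates and the reason for counting two techniques follow: "Assuming an α of 0.05 and 80% power, and since two irradiation techniques are evaluated". The resulting size is then stated in these words: "the study should include at least 58 subjects to ensure adequate power and compensation for possible loss of patients during the protocol". Sidedness, the split between techniques and the loss rate are not given.
- **Section 2.8.2 (Statistical Methods):** "The incidence of perfusion defects on follow-up cardiac SPECT will be calculated based on the number of patients" whose summed scores rise by the specified amount from baseline. Nothing further is said about inference on that incidence. The other methods are a rank-sum comparison of scans between time points with Bonferroni adjustment, a Spearman correlation of 6-month changes with irradiated structures, and regressions on cardiovascular risk factors.
- **Section 2.8.3:** the study is expected to demonstrate that both techniques prevent early and medium-term defects.
- **Section 4 (Conclusions):** "If the hypothesis of the absence of perfusion defects is confirmed", the two techniques could become new references. It adds that "if these techniques show no negative impact, specific post-irradiation monitoring will probably no longer be necessary".
- **Section 2.1:** the study is labelled a nonrandomized, descriptive pilot.

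**The concern.** Significance level and power have meaning only for a test, and the contrast that was sized is 17% against 0%. The methods section assigns no test, interval or criterion to that contrast. The rank-sum comparison does not fill the gap, because a non-significant change in scores shows neither that defects are absent nor that their incidence is below 17%.

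The target itself adds to the difficulty. A true rate of exactly 0% cannot be established by any finite sample, so the article describes a hypothesis as confirmable without saying what would confirm it. What counts as confirmation could then be settled after the results are known. This is the primary endpoint, and the Conclusions connect it, in hedged terms, to the need for monitoring after irradiation.

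**Working it through.** **Inputs.** Reference incidence p0 = 0.17, target p1 = 0, α = 0.05, power 0.80, N = 58 including an unstated allowance for loss (all Section 2.8.1). I read 17% as the incidence to be improved upon. A group size of 29 per technique assumes an even split of 58; the article states no split.

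**1. The plan's own figure.** The one-sample normal approximation is n = p0q0[z_α + z_β√(p1q1/(p0q0))]² / (p0 − p1)². With p1 = 0 the z_β term vanishes and n = z_α² × q0/p0.

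| Version | Per technique | Two techniques |
|---|---|---|
| One-sample, two-sided: 1.960² × 0.83/0.17 = 18.8 | 19 | 38 |
| One-sample, one-sided: 1.645² × 0.83/0.17 = 13.2 | 14 | 28 |
| One-sample, two-sided, α 0.025 per technique: 2.241² × 0.83/0.17 = 24.5 | 25 | 50 |
| Two-sample pooled, two-sided | 42 | 84 |

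None of these gives 58 directly. It can be reached with an assumed loss, for example 50/(1 − 0.14) ≈ 58 or 38/(1 − 0.34) ≈ 58. So 58 is not verifiable from the stated inputs, but it is not shown to be wrong, and the point does not depend on it.

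**2. What zero observed defects would show.** The exact two-sided 95% upper limit after 0/n is 1 − 0.025^(1/n).

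- 0/58: 1 − 0.025^(1/58) = 6.2%
- 0/29: 1 − 0.025^(1/29) = 11.9%

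The chance of seeing no defect when the true rate is p is (1 − p)^n. For p = 2% it is 0.98^58 = 0.31 and 0.98^29 = 0.56. For p = 1% and n = 58 it is 0.99^58 = 0.56. A clean result is therefore quite compatible with a non-zero rate.

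**3. What an interval against 17% would give at the planned size.** Clopper-Pearson two-sided 95% upper limits:

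| Defects / evaluable | Upper limit | Below 17%? |
|---|---|---|
| 4/58 | 16.7% | yes |
| 5/58 | 19.0% | no |
| 4/56 | 17.3% | no |
| 3/50 | 16.6% | yes |
| 4/50 | 19.2% | no |
| 0/29 | 11.9% | yes |
| 1/29 | 17.8% | no |

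With all 58 evaluable, the rule allows at most 4 defects. The exact one-sided size is P(X ≤ 4 | 58, 0.17) = 0.022. Power is 0.97 at a true rate of 3% and 0.84 at 5%. The allowed count changes with the number evaluable, so the criterion has to be the limit and not a fixed count. For 29 patients only 0/29 would pass, which makes a success criterion per technique a demand for zero events.

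**The case against.** The strongest reply is that this is a condensed article. The choice of interval, test and cut-off is commonly left to the full protocol or analysis plan, and the study is labelled descriptive and a pilot, which fits a calculated incidence. Both parts have weight. Nothing can be said here about documents not shown, and the absence of a named interval would not by itself be a finding.

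What remains is a mismatch inside the article. A powered contrast and confirmatory expectations stand beside a purely descriptive primary analysis. The pilot label does not resolve this: it fits Section 2.8.2 but not Sections 2.8.1, 2.8.3 and 4.

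Two stronger readings are tempting and should be resisted. A reader might infer that the plan will declare defects absent and end monitoring. Section 4 does not say so: its statements are conditional and hedged, and they are neither a decision rule nor an analysis step. A reader might also infer that a single defect, perhaps from one false-positive scan, would fail the trial. No section states such a rule; 0% appears as the aim of the dose reduction and as the planning alternative.

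**Conclusion.** The concern holds as an inconsistency within the article. The contrast that justifies the sample size has no matching analysis, while the expected conclusions need one. Followed as written, a result of no observed defects could be read as absence of defects, although 0/58 leaves rates up to 6.2% compatible with the data, and 0/29 leaves rates up to 11.9%.

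These limits assume that all patients counted are evaluable, and the second assumes an even split. With the losses that Section 2.8.1 anticipates, both limits would be higher. The finding does not rest on whether 58 can be reproduced.

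**What to change.** **Section 2.8.2.** Make the primary analysis the patient-level proportion with a new defect by 12 months among evaluable patients, with an exact Clopper-Pearson 95% interval. Base the conclusion on whether the upper limit lies below 17%, not on a fixed count; for illustration, at most 4 defects if all 58 are evaluable and 3 if 50 are. State that the pooled result governs. Report each technique with its own interval as descriptive, so that a pooled success is not presented as proof for both.

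**Sections 2.8.1, 2.8.3 and 4.** Replace the aim of 0%, the expectation of demonstrating avoidance by both techniques, and the wording about confirmed absence with a statement that the incidence is below 17%. Limit the remark on monitoring to what the upper limit supports.

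**Alternative.** Keep the descriptive pilot design, report the interval, and remove the confirmatory wording.

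**Cost.** Some sentences in four sections and a more modest claim. The change itself requires no extra patients or scans.

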#### 2.3.3. Follow-Up Phase

The follow-up will consist of cardiac gated-SPECT at 3 months, 6 months, and 12 months after the end of radiotherapy, in addition to the usual follow-up.

Before these examinations, a consultation with a nuclear medicine physician will be carried out, which will allow the collection of clinical data, including details of eventual side effects.

If a reversible perfusion defect is detected during the follow-up period, the patient will be referred to a cardiologist for exploratory coronary angiography and, if necessary, transcutaneous angioplasty.

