### 2.4. Practical Implementation of Cardiac SPECT

Cardiac SPECT will be obtained using a dedicated CZT camera (D-SPECT, Spectrum Dynamics Medical, Caesarea, Israel). According to the study protocol, patients will be scheduled to undergo cardiac SPECT before and at 3, 6, and 12 months post-irradiation. Stress electrocardiogram (ECG)-gated SPECT will be performed after infusion of 3 MBq/kg 99mTc-tetrofosmin (Myoview^®^, General Electric Healthcare, Chicago, IL, USA) at peak pharmacological stress with regadenoson (single dosage: 400 µg; Rapiscan^®^, GE Healthcare, Chicago, IL, USA). Intake of xanthic bases such as caffeine will be discontinued 24 h before cardiac SPECT. Rest ECG-gated SPECT will be performed on the same day, 4 h after stress ECG-gated SPECT, with administration of 8 MBq/kg 99mTc-tetrofosmin only if stress ECG-gated SPECT shows abnormalities.

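### The Wilcoxon rank-sum test planned for comparing SPECT results between visits ignores the pairing within patients; it is conservative and can lose much of its power, although the primary incidence is unaffected

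*Protocol article*

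**What the plan says.** The design is one of repeated measures. Section 2.4 states that "patients will be scheduled to undergo cardiac SPECT before and at 3, 6, and 12 months post-irradiation", and section 2.3.3 repeats the follow-up visits: "The follow-up will consist of cardiac gated-SPECT at 3 months, 6 months, and 12 months after the end of radiotherapy". Section 2.7.2 sets the contrast within the patient: "Postradiotherapy cardiac SPECT will be compared to baseline to assess changes in cardiac perfusion".

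Section 2.8.2 then does two separate things. First it defines the incidence as a count: "The incidence of perfusion defects on follow-up cardiac SPECT will be calculated based on the number of patients with an increase in SSS or SRS" that meets a segment-level threshold between the scans before and after radiotherapy. Next it names a test: "For comparison among cardiac SPECT results at different time points, the Wilcoxon rank-sum test will be used". A Bonferroni correction follows, without the number of comparisons. No paired test is named anywhere for the comparison between visits.

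The primary endpoint (2.5.1) is the occurrence of defects over the three follow-up visits, and the sample size (2.8.1) is argued in terms of that incidence, from about 17% to a target of 0%.

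**The concern.** The rank-sum test treats the baseline scans and the follow-up scans as if they came from different people. Stable differences between patients then count as noise, although comparing each patient with herself would remove them. The p-value does not have its nominal meaning, and when a patient's scores are positively correlated across visits the test rejects too seldom.

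The direction matters. Section 2.8.3 expects the trial to show that both techniques avoid new defects, and section 4 draws consequences from their absence. A score comparison that tends towards non-significance leans the same way. It is also the only hypothesis test that the article names for change in perfusion between visits.

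**Working it through.** **Inputs from the article.** Four scans per patient (2.4); 58 patients (2.8.1); 17% as the anticipated defect rate (2.8.1); overall alpha 0.05 with Bonferroni (2.8.2); summed scores from 0 to 68, with 0 normal (2.7.1). The article gives no power figure for this comparison, so there is none to reproduce.

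**Assumptions, not in the article.** Three comparisons with baseline, so alpha = 0.05/3 = 0.0167; all 58 patients complete; the within-patient correlation, the share of abnormal baselines and the size of the change are varied below.

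**1. Why the type I error falls.** With n patients measured twice, the rank-sum statistic is driven by the difference in mean ranks. For paired data its variance is approximately (1 − ρs) times the variance that the test assumes, where ρs is the rank correlation between visits. For bivariate normal scores ρs = (6/π)·arcsin(ρ/2). The true size at nominal two-sided 0.05 is then about 2·[1 − Φ(1.96/√(1 − ρs))].
- ρ = 0.3: ρs = 0.288, √(1 − ρs) = 0.844, 1.96/0.844 = 2.32, size about 2.0%.
- ρ = 0.5: ρs = 0.483, √(1 − ρs) = 0.719, 1.96/0.719 = 2.73, size about 0.6%.
- ρ = 0.7: ρs = 0.683, √(1 − ρs) = 0.563, 1.96/0.563 = 3.48, size about 0.05%.

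Simulation (10,000 runs, n = 58) agrees: 2.1%, 0.7% and 0.1% for rank-sum, against 4.8%, 5.2% and 5.3% for signed-rank.

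**2. Power with normal scores**, shift 0.4 SD, alpha 0.0167. For ρ from 0.5 to 0.9, rank-sum power is about 24% to 33% and signed-rank power 70% to 100%. For a 0.5 SD shift rank-sum reaches 61% to 73% (signed-rank 89% to 100%), so larger shifts are still often detected.

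**3. Power with scores that are mostly zero.** Suppose a share b has a stable abnormal baseline and 17% gain a new defect. The expected number with a score above 0 is 58b at baseline and 58b + 0.17 × 58(1 − b) afterwards:
- b = 0: 0, then 9.9
- b = 10%: 5.8, then 14.7
- b = 30%: 17.4, then 24.3
- b = 60%: 34.8, then 38.7

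The rank-sum test sees two groups that look more and more alike. A paired test sees about 10 patients rising and none falling, whatever b is. With 10 of 10 rising, the exact signed-rank p-value is 2 × 0.5^10 = 0.002.

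Simulated power at n = 58, alpha 0.0167, 17% new defects, no reading noise:

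| Abnormal at baseline | Rank-sum, defects add 3–6 points | Rank-sum, defects add 4–8 points | Signed-rank |
|---|---|---|---|
| 0% | 95% | 94% | 81–95% |
| 10% | 38% | 45% | 81–95% |
| 30% | 6% | 11% | 81–95% |
| 60% | 1% | 4% | 81–95% |

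The signed-rank range reflects whether zero changes are dropped (lower end) or kept in the ranking by Pratt's method (upper end).

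**4. Sensitivity.** With a 15% chance of a one-point reading error, rank-sum power is 31%, 7% and 2% at b = 10%, 30% and 60%. Signed-rank has 53% to 59% with Pratt's method and 79% to 83% with zeros dropped, so neither way of handling zeros is better in every case. With 27% new defects (no noise, alpha 0.05), rank-sum power is at least 76% at every b tried.

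**The case against.** The strongest reply is that the primary result does not pass through this test. Incidence is counted from each patient's own change. At a true rate of 17%, about 0.17 × 58 = 10 patients would be counted, provided their changes meet the rule, whatever the rank-sum p-value. The chance of counting none would be 0.83^58, about 0.00002. This stands in full.

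A reader might infer that real perfusion loss would usually be missed. The documents do not support that. They give no correlation, no rate of abnormal baselines and no reading error, and across plausible values rank-sum power runs from near 0% to near 100%. If all baselines are 0 and reading is free of noise, it is no worse than the signed-rank test.

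A reader might also infer that a non-significant result will be declared proof of no defects. No section says so: the stated target is an incidence. That reading is a risk to guard against, not part of the plan.

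Three further replies stand in part. The study calls itself a descriptive pilot (2.1), which lowers the stakes but does not make the named test suit the data. The division of alpha by three is an assumption: all pairs among four visits would be six comparisons, or 0.05/6 = 0.0083. And the wording may be a slip for signed-rank; if so, the text still prescribes the wrong analysis and needs correcting.

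Against the benign case of all-zero baselines, Table 1 does not exclude coronary disease or an abnormal baseline scan, and a score of 1 includes equivocal findings (2.7.1). Such a cohort cannot be presumed.

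**Conclusion.** The concern holds for the supporting comparison between visits. Section 2.8.2 names an independent-samples test for data that sections 2.3.3, 2.4 and 2.7.2 show to be paired. That mismatch needs no assumption. The direction of the error (conservative, towards no change) needs only positive correlation between scans of the same patient, which is to be expected. Its size is not fixed by the documents: under the illustrative assumptions, power at alpha 0.0167 ranges from about 95% down to 1% as abnormal baselines rise from 0% to 60%, where a paired test keeps about 81% to 95%. The primary incidence is unaffected. This is an error to correct before analysis, but it does not undermine the primary endpoint.

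**What to change.** In section 2.8.2, replace the rank-sum test with the Wilcoxon signed-rank test on each patient's change from baseline at 3, 6 and 12 months. State in advance how zero changes are handled, and state that Bonferroni is applied over those three comparisons. Add that a non-significant result will not be read as evidence of no perfusion change.

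The cost is two or three sentences. The data, visits and number of patients stay the same.

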#### 2.8.3. Project Duration and Expected Outcomes

The estimated period of inclusion will be one year. The estimated study completion date will be the end of 2023. The follow-up duration will be one year. The complete duration is estimated to be two years.

The study is expected to demonstrate that both radiotherapy techniques studied avoid the appearance of early- and medium-term perfusion defects. For this purpose, this trial proposes to reinforce the methodology of the previous studies by including a significant number of patients and by performing cardiac SPECT that follows a reversible abnormality detection protocol (resting and stress phases) and is administered at a frequency that covers the other data in the literature.

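### Bonferroni on the SPECT comparisons over time works against detecting perfusion loss, although the trial hopes to conclude that there is none

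*Protocol article*

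**What the plan says.** Section 2.8.2 of the protocol article contains two adjacent sentences: "For comparison among cardiac SPECT results at different time points, the Wilcoxon rank-sum test will be used", followed by "The Bonferroni technique will be applied to account for multiple comparisons". The same section sets the threshold: a p "value of 0.05 will be considered indicative of statistical significance". It does not list which comparisons form the Bonferroni family. Section 2.7.2 describes comparing each post-radiotherapy scan with baseline, and scans are planned at 3, 6 and 12 months.

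The primary endpoint (section 2.5.1) is the occurrence of perfusion defects at those visits. Section 2.8.2 obtains the incidence by counting patients whose segment scores rise past a fixed threshold. The article attaches no test, confidence limit or maximum tolerable rate to that count.

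The intended message is one of absence. Section 2.8.3: "The study is expected to demonstrate that both radiotherapy techniques studied avoid the appearance of early- and medium-term perfusion defects". Section 4: "if these techniques show no negative impact, specific post-irradiation monitoring will probably no longer be necessary".

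**The concern.** Bonferroni limits the chance of wrongly declaring a difference. In this trial a difference between baseline and follow-up is the harm, and the result hoped for is that there is none. The costly error is to overlook real perfusion loss, and lowering the per-test threshold makes that error more likely.

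A moderate rise in defects could then appear in the report as not significant after correction. Beside it would stand a conclusion that, in section 4, is linked to calling the techniques new references and to dropping specific cardiac monitoring. The point is separate from whether a rank-sum test suits repeated scans of the same patients. It remains if a paired test is used, which is why the check below uses one.

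**Working it through.** **Inputs from the article.** Section 2.8.1 gives the sample size of 58, the design values ("Assuming an α of 0.05 and 80% power") and the 17% planning incidence. Section 2.3.3 gives three follow-up scans. The 58 is taken as given: it cannot be reproduced without the design, sidedness and loss rate behind it, and nothing here depends on its derivation.

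**Assumptions.** All 58 patients are scanned. Affected patients worsen and nobody else changes. The test is a two-sided exact signed-rank test of one follow-up scan against baseline. The family is three comparisons (each follow-up against baseline, the natural reading of section 2.7.2) or, at the other extreme, six (all pairs of four scans). A true incidence of 10% is added to the 17% as a lower value of interest.

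**Step 1: worsened patients needed.** If all k non-zero changes are worsenings, p = 2 × 0.5^k. This gives 0.0625 for k = 5, 0.031 for k = 6, 0.0156 for k = 7 and 0.0078 for k = 8. The thresholds are 0.05, 0.05/3 = 0.0167 and 0.05/6 = 0.0083. The smallest significant counts are therefore 6, 7 and 8 of 58 (10%, 12% and 14%).

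**Step 2: miss rate at one visit.** Miss = P(Binomial(n, incidence) ≤ k − 1).

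| n, true incidence | Unadjusted (k = 6) | Three comparisons (k = 7) | Six comparisons (k = 8) |
|---|---|---|---|
| 58, 17% | 5.6% | 11.6% | 20.8% |
| 58, 10% | 47.1% | 64.0% | 78.0% |
| 50, 17% (assumed loss of 8 patients) | 12.6% | 23.1% | 36.7% |

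**Step 3: miss at all three visits.** The hoped-for claim covers all three visits, so a false reading of no change needs a miss at each. If visits were independent, the single-visit rate is cubed. If the same defects persist throughout, it is unchanged.
- 10% incidence, three comparisons: 0.640³ = 26% up to 64%. Unadjusted: 0.471³ = 10% up to 47%.
- 17% incidence, three comparisons: 0.116³ = 0.2% up to 12%. Unadjusted: 0.056³ = 0.02% up to 6%.

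**Step 4: check without the sparse-defect assumption.** Under a normal approximation, a test with 80% power at two-sided 0.05 has a standardised effect of 1.960 + 0.842 = 2.802. With three comparisons the critical value is 2.394, so the miss rate is Φ(2.394 − 2.802) = 34%. With six it is Φ(2.638 − 2.802) = 44%. Unadjusted it is 20%. The direction is the same.

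**Step 5: what the count would show.** Suppose 6 of 58 worsen and none improves. The exact p is 0.031, which is significant unadjusted but not at 0.0167. The exact one-sided 95% upper limit for 6 of 58 is 19.4%, above the 17% planning rate. For 0 of 58 it is 1 − 0.05^(1/58) = 5.0%.

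**The case against.** A reader might infer that the plan will treat a non-significant Wilcoxon result as proof of no negative impact, and so that Bonferroni biases the primary conclusion. The article does not say this. Its primary outcome is a count, its stated objective is an incidence of 0%, and its concluding language is about the absence of defects. Bonferroni does not alter a count. In the scenarios above, 6 worsened patients who meet the scoring threshold would be reported as a 10% incidence, in plain view and contrary to the objective. With a true 10% incidence, the chance of counting no defect at a given visit is 0.9^58 = 0.2%. This objection stands and limits the point.

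A reader might also argue that a claim which must hold at all three visits needs no alpha adjustment, so that Bonferroni is formally wrong. That rule applies when each rejection supports the claim and all must reject. Here a rejection signals harm, and one significant visit would undermine the claim. That is an ordinary at-least-one family, for which correction is permissible. Leaving harm tests unadjusted is a judgement about which error matters more.

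Three further objections hold in part. At the planning incidence of 17% the loss is modest: single-visit power is 94% unadjusted, 88% with three comparisons and 79% with six, against a planned 80%. The family is not defined and may be set in an analysis plan that is not shown, so the six-comparison figures are an outer case. Finally, removing Bonferroni does not demonstrate absence, since at 10% incidence the unadjusted test still misses 47% of the time at one visit.

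What remains is that the article affirmatively places the correction next to the only tests named for change over time, and for the stated aim it pushes the wrong way.

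**Conclusion.** The concern holds as a point about the direction of the correction. For a trial that hopes to report no perfusion loss, Bonferroni on the baseline-to-follow-up comparisons raises the chance of missing loss. With three comparisons, the single-visit miss rate roughly doubles at 17% incidence and rises by about 17 percentage points at 10%. Across all three visits at 10%, the range moves from 10–47% to 26–64%, depending on how far defects persist.

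These figures rest on full scanning of 58 patients, worsening changes only, a paired exact test and an assumed family of three. Figures for the rank-sum test as named are not relied on, because they depend heavily on the assumed baseline scores.

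The article does not support the stronger claim that the primary result is wrong or that non-significance has been adopted as the success rule. This is a worthwhile, low-cost improvement to a descriptive pilot study.

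**What to change.** In section 2.8.2:
- Report the three comparisons of baseline with 3, 6 and 12 months at an unadjusted 0.05, and do not test pairs of follow-up scans.
- Keep Bonferroni for exploratory analyses in which a positive association would be claimed, such as the dose correlations and risk-factor regressions.
- State that a non-significant comparison is not evidence of no impact.
- Base any statement of no negative impact on the counted incidence at each visit with its exact upper confidence limit. As a guide, the one-sided 95% limit is 5.0% for 0 of 58 and 19.4% for 6 of 58. If technique-specific statements are made, 0 of 29 (an assumed equal split) gives 9.8%.

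The last item is essential, because removing Bonferroni alone would not show absence.

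The cost is wording only, with no extra patients or scans. The downside is a higher chance of a false signal: with three independent tests at 0.05, the chance of at least one is 1 − 0.95³ = 14%, counting changes in either direction. That is the cautious direction for a claim of no harm.

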#### 2.5.2. Secondary Endpoints

The secondary endpoints are as follows:-The incidence of left ventricular wall motion disorder and LVEF quantification on follow-up cardiac SPECT scans at 3-, 6-, and 12-months post-irradiation.-Measurement of the delivered doses to the cardiac volumes and their substructures.-The influence of cardiac risk factors on postradiation myocardial perfusion.-Assessment of the influence of chemotherapy/trastuzumab/trastuzumab emtansine exposure on postradiation myocardial perfusion.-Assessment of tumor-bed boost location on cardiac dose.

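### The risk-factor analysis moves from univariate linear regression to a multivariable proportional hazards model with no defined time-to-event outcome and, at the planning rates, 0 to about 10 events

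*Protocol article*

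**What the plan says.** All references are to the protocol article.

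- **Section 2.8.2, first step:** "A univariate linear regression analysis will be conducted to investigate the association between various cardiovascular risk factors and alterations in cardiac SPECT defects".
- **Section 2.8.2, next sentence on the same question:** "Standard proportional hazard regression analysis will be used for the subsequent multivariate analysis". No event, time origin or censoring rule is named.
- **Sections 2.3.3 and 2.5.1:** SPECT is repeated at 3, 6 and 12 months, and the primary outcome is whether a perfusion defect occurs. Section 2.8.2 computes incidence by counting patients whose SSS or SRS rises by a set amount.
- **Section 2.5.2:** the influence of cardiac risk factors is a secondary endpoint. So is the following: "Assessment of the influence of chemotherapy/trastuzumab/trastuzumab emtansine exposure on postradiation myocardial perfusion".
- **Section 2.8.1:** "the study should include at least 58 subjects to ensure adequate power", with a reference incidence of about 17% and a target of 0%. Section 2.8.3 expects both techniques to avoid perfusion defects.

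**The concern.** The multivariable step is introduced as the continuation of the univariate one, so a reader would expect the same association before and after adjustment. The two models cannot deliver that. A linear coefficient is a difference in mean score change; a hazard ratio compares rates of a first event. If a risk factor looked important in one and not in the other, nobody could tell whether adjustment, the change of outcome or the change of scale was responsible.

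The hazard model also depends on events, and the trial is designed in the hope of seeing none. The closer the trial comes to its own target, the less the only stated multivariable analysis can say about cardiac risk factors.

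**Working it through.** **1. Do the two models fit one outcome?** Linear regression takes a numeric response, here most naturally the change in SSS or SRS. Proportional hazards regression takes a time and an event indicator. The article defines a score change and a yes/no defect at fixed visits, but no time to event. A detected defect could be dated only to one of three visits. The two sentences therefore cannot describe one analysis of one outcome.

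**2. The plan's own figure.** The 58 in section 2.8.1 does not follow from the stated inputs alone. One route that reaches it is a one-sample test of 0% against 17%, with alpha halved to 0.025 for two techniques: n = 2.241² × 0.17 × 0.83 / 0.17² = 24.5, so 25 per technique and 50 in all. Then 50/58 = 0.862, a loss allowance of about 14%. No loss rate is stated, so 58 is not shown to be wrong and is taken as given.

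**3. Events implied.**
- Target: 58 × 0 = 0.
- Reference: 58 × 0.17 = 9.9, or about 10. That is 4.9 events per covariate with two covariates, 2.0 with five and 1.4 with seven.
- Illustration between the two, 5%: 58 × 0.05 = 2.9, with a 0.95^58 = 5% chance of none.

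**4. Precision with 10 events** (Schoenfeld approximation, two-sided 5%, exposure prevalence p assumed to be 20–50%).
- Power = Φ(√(10·p(1−p))·ln HR − 1.96). HR 2: 14% (p = 0.2) to 19% (p = 0.5). HR 3: 28% to 41%.
- HR detectable with 80% power = exp(2.80/√(10·p(1−p))): 9.2 (p = 0.2) to 5.9 (p = 0.5).
- 95% interval, as a factor either way = exp(1.96/√(10·p(1−p))): 4.7 to 3.5.
- Events needed for 80% power = 7.85/(p(1−p)·(ln HR)²): 66–103 for HR 2 and 27–41 for HR 3.

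**5. Risk of an infinite estimate.** If none of e events falls among the exposed, the hazard ratio estimate runs to zero. For k independent binary covariates with no effect, the chance that this happens for at least one is 1 − (1 − (1−p)^e)^k. The article gives neither k nor p, so both are varied.

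| Events | Covariates | p = 0.2 | p = 0.3 | p = 0.4 | p = 0.5 |
|---|---|---|---|---|---|
| 10 | 2 | 20% | 6% | 1% | 0.2% |
| 10 | 7 | 55% | 18% | 4% | 0.7% |
| 5 | 2 | 55% | 31% | 15% | 6% |
| 5 | 7 | 94% | 72% | 43% | 20% |
| 2 | 7 | >99% | 99% | 96% | 87% |

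Simulated Cox fits agree in pattern (58 patients, three visits, assumed prevalences of 15–50%, 300 runs per setting). At 17% incidence, no finite estimate arose in 4% of fits with two covariates, 31% with four and 48% with seven. At 5% incidence the shares were 63%, 88% and 97%. At 0% incidence every fit fails.

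**The case against.** The strongest reply is that this is one secondary analysis in a study that section 2.1 calls a descriptive pilot, and that the event definition, censoring rule and covariate list normally belong in an analysis plan that is not shown. Most of that stands, and it limits how serious the point is. It does not remove it. Supplying a time-to-event definition elsewhere would still leave the unadjusted result on a linear scale and the adjusted one on a hazard scale, because the article fixes both methods.

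Several stronger readings are tempting, and the document does not support them.

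- **The risk-factor objective cannot be estimated at all.** This is literal only at or near zero events, and only for the hazard model. With about 10 events, one or two covariates usually give finite, very imprecise estimates. The linear step does not need events: each segment is scored 0–4 and the event threshold is at least 3 points in one segment or 2 in at least two, so scores can vary below it. Nothing in the article says that the changes are mostly zero.
- **The drug-exposure objective fails too.** Section 2.8.2 ties the regression to cardiovascular risk factors and names no model for chemotherapy, trastuzumab or trastuzumab emtansine. Its dependence on the hazard model is an inference.
- **Three visit times rule out proportional hazards.** All patients share the visit schedule, and tie corrections or discrete-time versions are routine options. The fair criticism is that the outcome is undefined.
- **Ten events is a ceiling.** It is the planning reference. The Introduction cites 27–70% in earlier studies, which would give 58 × 0.27 ≈ 16 to 58 × 0.70 ≈ 41 events, but the trial does not plan on those rates.

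**Conclusion.** The point holds in a limited form and should be fixed. As written, the univariate and multivariable steps do not share an outcome or scale, and the second has no defined outcome. At the planning rates it would have 0 to about 10 events. Hazard ratios would be unreliable with more than one or two covariates, imprecise even then, and non-existent if the 0% target is met.

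The event range rests on the article's 58 patients, 17% and 0%. The power and infinite-estimate figures rest on assumed prevalences and covariate counts. They show direction and order of size; they do not forecast this trial. The effect is confined to the secondary cardiac-risk-factor objective. The primary incidence, a count of patients, is unaffected.

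**What to change.** Replace the proportional hazards sentence in section 2.8.2 so that both steps use one outcome and one model family. Label the analysis exploratory and limit the multivariable model to one or two prespecified covariates. Either of two routes would do:

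1. Carry the linear regression of the SSS/SRS change score into the multivariable step. This keeps the graded score and remains usable with no events, provided that the scores vary.
2. Take new defect by 12 months as the outcome in both steps, with Firth-penalised or exact logistic regression, or a discrete-time model over the three visits if timing matters. If events are very few, give descriptive tables with exact intervals only; this route yields no association estimate at zero events.

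If the drug-exposure objective is meant to use the same model, say so, and count those exposures within the covariate limit.

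The cost is a change of wording and fewer covariates in one secondary model. No extra patients, scans or data are needed.
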